# **7. NUTRITIONAL SUPPLEMENTATION**

Guardians will be instructed in proper storage and consumption of the allocated nutritional supplement products. Refer to Annex 11 for the composition of these products.

## **7.1 RUTF (Plumpynut®)**

Participants allocated to receive Plumpynut® will receive 14 sachets, one for each day. One package of Plumpynut® provides 500 kcal and vitamins and minerals, including vitamin A, B, C, selenium, zinc, folic acid, copper, iron. Ingredients used for the manufacturing of Plumpynut® include peanuts and milk components. (see annex 1)

## **7.2 MNP (MixMe®)**

The MNP contains the micronutrients recommended by WHO, UNICEF, and the WFP (see Annex 11).[25] In order to be approximately comparable with the micronutrient composition of RUTF the daily quantity is doubled. Participants allocated to receive MixMe® will receive 28 sachets, two sachets for each day of supplementation.

## **7.3 Control group**

For the purpose of this study, it is not practically feasible to design and manufacture a placebo for RUTF or the MNP. Children randomly assigned to the control group will receive equivalent care and follow-up as the children assigned to a study group receiving supplementation. The only difference is that they will not receive a nutritional supplement (current clinical practice does not include nutritional supplement).

---

\*One nurse assistant will be selected as study dispenser/treatment allocation (always will be the same person). The paragraph refers to randomization. It is only highlighting that no one except one individual will have access to the list in order to avoid anyone influencing the randomization of patients to treatment.

## 8. CLINICAL PROCEDURES AND METHODOLOGY

### 8.1 Study clinic procedures at day of inclusion (day-0)

After inclusion, study procedures on day-0 include:

- Baseline socio-demographic questionnaire with i) Socio-economic data (incl. education level of guardian, whether family is receiving food aid, average number of meals consumed prior to clinical visit, etc.) and ii) Demographics (name, age, address) (see annex f4-General questionnaire)
- Child health questionnaire, including breastfeeding practices, duration of illness prior to clinical visit
- Anthropometric measurements, including weight, height, and MUAC
- Medical examination, including fever, concomitant illnesses, bilateral oedema
- Laboratory exams: haemoglobin, if indicated
- Counselling on the importance of providing their child with an extra meal during the convalescence period

**Treatment of study diseases:** All children will receive standard care and treatment according to current MoH/MSF medical protocols. This includes provision of zinc supplement to children with diarrhoea according to WHO and MSF recommendations.

**DOT:** For any drugs prescribed by the MoH OPD clinician, participants will be responsible for retrieving these drugs from the MoH pharmacy, as per normal practices. The first dose of prescribed drugs will be taken in the presence of a study nurse.

In addition to the three study diseases, participants presenting to the study clinic for follow-up visits (scheduled and unscheduled) will be cared for by the study clinic for any illnesses not requiring lengthy or complicated follow-up. Children suspected to have a serious illness will be referred to the MoH OPD or other appropriate services.

### 8.2 Follow-up schedule

After inclusion, the guardian will be instructed to return to the study clinic whenever the child is ill unless an emergency dictates attendance at a closer medical facility. Study staff will visit the OPD waiting room for study participants that might be mistakenly waiting there instead of going to the study clinic. MoH OPD will be asked to immediately refer all study participants to the adjacent study clinic.

In order to record any diagnoses and treatments prescribed when visiting a non-study clinic (i.e. private clinic, traditional healer, etc), participants be given a 'study card' describing the nature of the study and the need for non-study clinical staff to record on the card any new clinical data and medications provided or prescribed. Participants will be asked to actively provide this study card whenever consulting a non-study clinic. The decision to record diagnoses from a non-study clinic for study purposes will be made on individual basis, considering reliability and relevance of diagnosis (See annex f6 for the Patient Take-Home Card).

A number of procedures will be repeated during the follow-up visits at the study clinic. Patients will have a follow-up form for procedures to be ticked off when completed (see annex f3 - Study Follow-up Form).

Table 1 below gives an overview over all study procedures.

**Table 1: Schedule of study procedures**

| Procedure               | Day 0 | Day 14 | Day 28 and every 4 weeks after | Unscheduled visits | Final visit (day 168) |
|-------------------------|-------|--------|--------------------------------|--------------------|-----------------------|
| Informed consent        | √     | -      | -                              | -                  | -                     |
| Randomisation           | √     | -      | -                              | -                  | -                     |
| Baseline questionnaire  | √     | -      | -                              | -                  | -                     |
| Child health, history   | √     | √      | √                              | √                  | √                     |
| Clinical examination*   | √     | √      | √                              | √                  | √                     |
| Follow-up questionnaire | -     | √      | √                              | -                  | √                     |
| Weight                  | √     | √      | √                              | -                  | √                     |
| MUAC                    | √     | √      | √                              | -                  | √                     |
| Height                  | √     |        | √                              | -                  | √                     |
| DOT                     | √     | -      | -                              | -                  | -                     |
| RUTF / MNP distributed  | √     | √      | √ §                 | √ §     |                       |

|                          |   |   |   |   |   |
|--------------------------|---|---|---|---|---|
| Compensation distributed | √ | √ | √ | - | √ |
|--------------------------|---|---|---|---|---|

\* Complete exam when diagnosed with an illness or otherwise deemed necessary, otherwise limited to a rapid exam, including assessing treatment side-effects and response

§ When indicated

**Questionnaires:** Questionnaires will be translated into local languages, back-translated and piloted for comprehension in the area of the study site. (See annex f4 for baseline questionnaire and annex f5 for follow-up questionnaire)

**Unscheduled visits:** If unscheduled visit occurs within 48 hours prior to a scheduled visit, the child will not need to return for that upcoming scheduled visit.

**Repeated supplementation:** Patients presenting with a new episode of a study disease will receive a new 14-day supplement, according to the intervention originally assigned. Though care and treatment will be available whenever ill, a child will not receive more than 14 days supplementation within any 28 day period. For example, a child receiving a new supplementation package on day-42 due to a newly diagnosed study disease cannot receive another supplementation package before day-70.

One reason to limit the distribution to a monthly frequency is to minimize potential bias related to the likelihood that children receiving Plumpynut® (a product known and recognized by the community) may be more likely to come forward for an unscheduled visit with the intention to receive additional distribution of supplementation.

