**Summary of study design**

This is a randomized controlled trial with three study groups each with 734 participants.

Children participating in this study will be randomised to one of three study groups to:

- A) Receive 14 days of RUTF supplementation with standard care and treatment
- B) Receive 14 days of Multi-micronutrient powder (MNP) supplementation with standard care and treatment
- C) Be included in a control group with standard care and treatment but not receiving nutritional supplementation

Individual follow-up will be 6 months. During this time, children included in the RUTF or MNP group will receive 14 days nutritional supplement, every time diagnosed with at least one of the three study diseases, not exceeding more than 14 days supplementation in any 28 day period. Children randomly assigned to the control group will receive equivalent care and follow-up as children receiving supplementation. The only difference is that they will not receive a nutritional supplement. Current clinical practice does not include nutritional supplement.

At recruitment written consent of the guardian is obtained. Baseline information will be collected and medical examination will be performed.

After 14 days and 28 days, and thereafter every month, the participant will be weighed and measured, medically checked and questioned about illness.

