## 2. STUDY OBJECTIVES

**The aim of the study is to** “To determine the *effectiveness* of 14 days nutritional supplementation (RUTF or MNP) given concurrently with the appropriate medical treatment, in children diagnosed with malaria and/or diarrhoea and/or LRTI in reducing the incidence of acute malnutrition and the incidence of the three study diseases compared to a control group.”

**The primary objective** is to determine the effectiveness of 14 days of RUTF supplementation versus no supplementation control group on the *incidence of acute malnutrition*

**Primary Hypothesis:** Supplementation for 14 days with RUTF, concurrent to appropriate medical treatment for malaria, and/or LRTI, and/or diarrhoea reduces the incidence of acute malnutrition compared to a control group during 6 months follow-up, amongst children 6-59 months of age with malaria and/or, LRTI and/or diarrhoea at time of recruitment.

**Secondary objectives** include:

Incidence of malnutrition

- i.) Determine the efficacy of 14 days MNP supplementation versus a control group and RUTF versus MNP on the incidence of acute malnutrition during 6 months follow-up,

Frequency of morbidity

- ii.) Determine the effect of 14 days supplementation on the *frequency of morbidity* (3 study diseases) during 6 months follow-up, comparing both intervention groups to the control group and comparing RUTF to MNP)

Weight changes immediately after intervention period, measured at day-14 and day-28

- iii.) Measure *mean weight change* (total change and rate (grams/kg/day) of change), comparing both intervention groups separately (RUTF and MNP) to control group
- iv.) Determine *frequency of ‘no weight gain and/or weight loss’*, comparing both intervention groups separately (RUTF and MNP) to control group
- v.) Assess if provision of 14 days of RUTF or MNP supplement promotes a sustained weight gain, measured after 28-days of follow-up, comparing both intervention groups separately (RUTF and MNP) to control group

Sub group analyses

- vi.) Children under 3 years of age at inclusion: Determine the effect of 14 days supplementation on the *incidence of acute malnutrition* and *frequency of morbidity* (3 study diseases) during 6-months follow-up, comparing children under 3 years of age to older children.

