## **8.5 Compliance**

Compliance regarding the consumption and acceptability of the nutritional supplements will be assessed only after the first 14 days of supplementation, through a questionnaire and collection of returned supplement sachets (used or unopened). The study dispenser will count and record the returned sachets (empty or unopened) after the questionnaire is completed.

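### Table 1 schedules supplement distribution at day 14, which the protocol's own cap of 14 days in any 28 forbids; the tick should be deleted

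*Protocol*

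**What the plan says.** Table 1 in Section 8.2 of the protocol lists the procedures by visit. Its row "RUTF / MNP distributed" has an unmarked tick at day 0 and another at day 14. The ticks for day 28 and later visits, and for unscheduled visits, carry a footnote limiting them to cases where distribution is indicated.

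The paragraph on repeated supplementation, just after the table, says that "a child will not receive more than 14 days supplementation within any 28 day period". Its example is a child supplied on day 42, who "cannot receive another supplementation package before day-70". It describes the limit as a monthly frequency, partly to reduce bias from families attending in order to obtain Plumpynut. The same cap is in the Executive Summary ("not exceeding more than 14 days supplementation in any 28 day period") and in Section 3.

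The course is 14 days in both arms. RUTF participants "will receive 14 sachets, one for each day" (Section 7.1), and MNP participants "will receive 28 sachets, two sachets for each day of supplementation" (Section 7.2). Section 8.5 has sachets returned and counted once the first 14 days are over.

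**The concern.** Read literally, Table 1 tells the dispenser to supply every child in the two supplement arms at day 14, two weeks after a full 14-day course was issued. The cap forbids this. The two statements stand in the same section, and one of them is the schedule staff would work from.

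At stake are the dose and timing of the first course. The primary hypothesis concerns 14 days of RUTF, and a second package at day 14 would double that. It would also remove the supplement-free interval before day 28. Objective v in Section 2 asks whether 14 days of supplement "promotes a sustained weight gain, measured after 28-days of follow-up". If the supplement ran up to the day before that weighing, the day-28 weight would show gain during supplementation and could not show whether gain lasts after it stops. The day-28 weight endpoints in Section 8.8.2 would be affected in the same way.

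**Working it through.** **Inputs**
- Length of a course: 14 days in both arms (Sections 7.1 and 7.2).
- Daily amount: one RUTF sachet of 500 kcal, or two MNP sachets (Sections 7.1 and 7.2).
- Cap: 14 supplemented days in any 28 (Executive Summary, Section 3, Section 8.2).
- Every child has a study disease at inclusion (Section 4.2), so a package is due on day 0 in both supplement arms.

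**Reproducing the protocol's example.** Suppose a first package is given on day *s* and a second on day *s + g*, with *g* between 14 and 28. The largest number of supplemented days in any 28-day window is 14 + (28 − *g*) = 42 − *g*. The cap requires 42 − *g* ≤ 14, so *g* ≥ 28. With *s* = 42, the earliest second package is on day 42 + 28 = 70, as the protocol states.

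**Applying it to day 0.** With *s* = 0, the earliest second package is on day 28.

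| Second package on day | Supplemented days in days 0–27 | Within the cap? |
|---|---|---|
| 14 | 42 − 14 = 28 | no |
| 21 | 42 − 21 = 21 | no |
| 27 | 42 − 27 = 15 | no |
| 28 | 42 − 28 = 14 | yes |

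**Size for one child, if the tick were followed**
- Supplemented days in days 0–27: 14 + 14 = 28, against 14 allowed.
- RUTF: 28 × 500 = 14,000 kcal, against 14 × 500 = 7,000 kcal.
- MNP: 28 × 2 = 56 sachets, against 14 × 2 = 28.
- Supplement-free days before the day-28 weighing: 28 − 28 = 0, against 28 − 14 = 14.

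**Which statement is wrong.** The cap appears three times, with a worked example and a reason. The tick has no support elsewhere.

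Three readings might rescue the tick, and none does:
- *A lost conditional mark.* A conditional package at day 14 still breaks the cap for any child supplied on day 0, even with a new episode.
- *A first supply split between day 0 and day 14.* Sections 7.1 and 7.2 give the sachets per course without saying that they are issued together, so this has to be inferred. But Section 8.2 speaks of packages, Section 8.5 has sachets returned after the first 14 days, and Section 2 treats the day-14 weight as taken once the intervention period has ended. A second instalment at day 14 does not fit these.
- *The sachet return.* This may be what the tick was meant to show, but the row is about distribution.

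**The case against.** The best reply is that this is an editorial slip. The operative rule is clear and repeated, and it stands directly below a table that is introduced only as an overview. One dispenser, always the same person, issues all supplements, so there is little room for divergent practice. The sachet and calorie figures only restate 28 days against 14, and they apply only if staff ignore the written rule. All of this is fair, and it is why the point is modest. However, the dispenser is also the only team member who knows the allocation, so a misreading would be systematic and hard for the blinded coordinator to notice.

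A second reply is that the conditional mark already works subject to the cap. The unscheduled-visit column carries it, although an unscheduled visit before day 28 is barred in the same way. A conditional day-14 tick could then serve a child who missed the day-0 package. That is logically possible, but the protocol describes no late first supply. For children supplied on day 0 as planned, nothing can be indicated at day 14.

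A third reply is that the table was machine-read and a superscript may have been lost. That cannot be excluded. It would weaken the literal instruction to supply every child, but the cell would still point to a package that the cap forbids.

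**Conclusion.** The concern holds. Table 1 calls for a distribution that the cap rules out for any child given the day-0 package. The tick is the error; it does not describe a second regimen. If it were followed, the first course would double from 14 to 28 days, and the 14 supplement-free days before the day-28 weighing would be lost. This assumes that the full 14-day supply is issued on day 0, which the protocol implies but does not say outright.

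The effect is conditional, and the protocol gives no basis for estimating how many children, if any, would be affected. The weight endpoints are secondary, with p-values treated as explorative (Section 9.3.3). The primary endpoint definition, significance level, power and sample size are untouched. The cell should be corrected because it governs dose and timing, and correcting it costs almost nothing.

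**What to change.** In Table 1, replace the day-14 tick in the distribution row with a dash. Adding the conditional footnote instead would leave the conflict in place for every child supplied on day 0. Day 14 then keeps its other procedures, with the sachet return and compliance questionnaire of Section 8.5.

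The dispensary allocation register (annex f9) is not among the documents available. If it does not already say so, add one line that no second package is issued before day 28.

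The cost is one table cell and at most one line in the register. Neither the design nor the analysis changes.

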## **8.4 Three study diseases**

Three diseases/morbidities are targeted during this study: malaria, diarrhoea, and LRTI. Clinical diagnoses will be made using existing standard MSF/WHO protocols and case definitions [26,27] A flow chart with to guide diagnosis and inclusion is detailed in Annex f7-diagnostics.doc.

- **Diarrhoea:**

The forms of diarrhoea include:

1. Acute diarrhoea, simple without blood: the passage of at least three liquid stools per day for less than 2 weeks
2. Persistent/chronic diarrhoea: diarrhoea beginning at least 14 days ago, and any period without diarrhoea has not exceeded two days. (WHO definition) [28]
3. Bloody diarrhoea

- **Lower Respiratory Tract Infection (LRTI)**

Refers to acute pneumonia:

- children presenting with cough or difficulty breathing **plus**
- Increased respiratory rate
  - Age 6–11 months: RR > 50 breaths /minute
  - Age 12 to 59 months: RR > 40 breaths /minute

- **Malaria, Plasmodium falciparum and other species**

- Fever or history of fever within 24 hours with positive malaria RDT result

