### **8.8.2 Secondary endpoints**

Secondary endpoints include

- Number of NNO's per study group in a period of 6 months
- Time to NNO
- Number of new events of a study disease in 6 months
- Weight change at 14 days and 28 days after study inclusion, and at end of study period
- Rate of weight change (grams/kg/day) at 14 days and 28 days after study inclusion, and at end of study period
- Proportion of children not gaining weight (including losing weight), measured at day-14 and day-28 after study inclusion.
- Proportion of children developing bilateral oedema
- Mortality: overall mortality, including the three study diseases and malnutrition.
- Morbidity, including the three diseases.
- Proportion of children with a reported cough at clinical visit

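### The six-month disease count pools scheduled visits with visits that unblinded guardians initiate and that earn product only in the supplement arms, so a real RUTF effect on illness could be attenuated or hidden

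*Protocol*

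**What the plan says.** Section 2 puts two outcomes in the aim: "reducing the incidence of acute malnutrition and the incidence of the three study diseases compared to a control group". The disease part is a secondary objective. Its endpoint in Section 8.8.2 is "Number of new events of a study disease in 6 months", and Section 9.3.3 treats p-values for secondary endpoints as exploratory. Neither section says at which visits an event must be found in order to count.

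Episodes can reach the data by three routes:

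- **Scheduled visits.** Table 1 plans history and clinical examination in all groups at day 14, day 28 and every four weeks to day 168.
- **Unscheduled visits.** Under Section 8.2 "the guardian will be instructed to return to the study clinic whenever the child is ill".
- **Outside providers.** Diagnoses noted on the study card are accepted case by case (Section 8.2).

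The product rule is in Section 8.2, under repeated supplementation: "Patients presenting with a new episode of a study disease will receive a new 14-day supplement", of the type originally assigned. For control children Section 7.3 says: "The only difference is that they will not receive a nutritional supplement". Section 6.2 states that participants are not blinded.

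The same part of Section 8.2 recognises a potential bias: children given the RUTF product, which the community knows, "may be more likely to come forward for an unscheduled visit with the intention to receive additional distribution of supplementation". The stated countermeasure is that "a child will not receive more than 14 days supplementation within any 28 day period".

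**The concern.** In the supplement groups the event being counted is also the event that earns product. In control it earns nothing. Table 1 and Section 11.1 tie the small compensation to scheduled visits, so product is the only study item on offer at an unscheduled visit, and only two of the three groups can receive it.

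If RUTF families bring in mild illness that control families would leave at home or take elsewhere, the RUTF count rises for a reason unrelated to how often children fall ill. The bias runs against RUTF. A true reduction in illness would look smaller or could vanish, and a null result on this objective could not be interpreted. RUTF against MNP is less exposed, because MNP families have the same kind of incentive. There the bias depends only on RUTF being the more sought-after product.

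Diarrhoea is the most exposed of the three diseases. Its acute form in Section 8.4 is "the passage of at least three liquid stools per day for less than 2 weeks", which in an outpatient clinic rests in practice on the guardian's account. Malaria needs a positive rapid test and LRTI a raised respiratory rate, but both are found only if the child attends. The endpoint on reported cough at a clinical visit has the same weakness if unscheduled visits enter it.

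**Working it through.** **The plan's own figures.** The protocol gives no expected rate, sample size or power for disease frequency, so there is no figure to reproduce. The 660 per group in Section 9.1 concerns malnutrition and does not bear on this point.

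**What the 28-day limit does.** Every supplemented child receives a package at day 0, so no further product can be earned for at least 28 of the 168 days, and again for 28 days after each later package. The incentive then returns. Packages could fall on days 0, 28, 56, 84, 112 and 140, six in all. The limit applies to packages, not to visits or counted diagnoses.

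**Effect on the rate ratio.** Let

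- RR be the true rate ratio, RUTF to control;
- s be the share of counted episodes that come from guardian-initiated visits;
- k be the ratio, RUTF to control, of presenting and being counted at such visits for the same illness.

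Then observed RR = true RR × [(1 − s) + s × k].

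The protocol gives neither s nor k, and both are assumed here. A true RR of 0.85 is also an assumption, chosen for illustration.

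| s | k = 1.10 | k = 1.20 |
|---|---|---|
| 0.25 | 0.85 × 1.025 = 0.87 | 0.85 × 1.05 = 0.89 |
| 0.50 | 0.85 × 1.05 = 0.89 | 0.85 × 1.10 = 0.94 |
| 1.00 | 0.85 × 1.10 = 0.94 | 0.85 × 1.20 = 1.02 |

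**Extra presentation that hides the effect completely.** Setting observed RR to 1 gives k = 1 + (1/RR − 1)/s.

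| True RR | k if s = 1 | k if s = 0.5 |
|---|---|---|
| 0.70 | 1.43 | 1.86 |
| 0.80 | 1.25 | 1.50 |
| 0.85 | 1.18 | 1.35 |
| 0.90 | 1.11 | 1.22 |

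So hiding a 10 to 30% reduction takes 11 to 43% more presentation if every episode comes from guardian-initiated visits, and 22 to 86% more if half do.

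**RUTF against MNP.** The same formula applies with k defined as RUTF relative to MNP. If both incentives are equally strong, k = 1 and the bias cancels.

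**Weight of diarrhoea.** Section 1.1 gives the 2009 clinic diagnoses in children under five as 1697 malaria, 2578 diarrhoea and 2816 LRTI. The diarrhoea share is 2578 / (1697 + 2578 + 2816) = 2578 / 7091 = 36%. This describes the clinic's caseload, not trial follow-up, and is only a rough guide.

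**The case against.** Much can be said for the plan. The protocol raises the risk itself and mitigates it. Its wording is cautious: it speaks of a possibility and does not predict that RUTF families will attend more. Section 6.2 blinds clinical staff, and two of the three diseases need an objective sign. Scheduled visits are the same in all groups, with reminders and tracing (Section 8.9). The endpoint is secondary and exploratory, the sample size rests on malnutrition, and a bias against RUTF cannot create a false claim of disease benefit.

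All of this stands and limits the importance of the point. It does not dispose of it. Blinded staff, rapid tests and respiratory rates limit false diagnoses, but they cannot recover true mild episodes that families never present, and later modelling cannot restore visits that were not made.

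A reader might infer that the disease count rests on guardian-initiated visits alone. The documents do not say so: the Executive Summary and Table 1 also look for disease at every scheduled visit. The 0.94 to 1.02 range is therefore the extreme case of s = 1.

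A reader might also infer that the scheduled-visit comparison should replace the all-visit count. That does not follow:

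- Seven looks in 168 days miss many short episodes between visits and measure something closer to point prevalence than the six-month frequency named in the objective.
- Table 1 allows product at scheduled visits from day 28 on when indicated, so diarrhoea reporting stays exposed there.
- The Table 1 footnote permits a rapid examination when no illness is apparent.
- An unscheduled visit in the 48 hours before a scheduled one replaces it.

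Finally, some of the reporting detail could sit in the statistical analysis plan, which is not at hand. The source of events, the product rule and its limit are fixed in the protocol.

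**Conclusion.** The point holds as a limited design weakness in a secondary, exploratory endpoint. The all-visit disease count is open to attendance that depends on the group. The protocol foresees this for RUTF, and its 28-day limit reduces it without removing it. The direction is against RUTF, clearly so in the comparison with control and less so with MNP.

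The size is unknown. With 10 to 20% more presentation in the RUTF group, a true rate ratio of 0.85 is attenuated to 0.89 to 0.94 when half of the episodes come from guardian-initiated visits. It reaches 0.94 to 1.02 only when all do. These ranges rest on assumed values of s, k and the true effect. The direction rests only on RUTF families attending more.

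The documents do not support a claim that the morbidity objective is invalid or that the primary result is threatened through this count.

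**What to change.** Keep the all-visit episode count as the measure of six-month frequency, and pre-specify beside it:

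- (a) a between-group comparison of study diseases found at the scheduled visits (day 14, day 28, then every four weeks to day 168), with the Section 8.4 disease checks applied in the same way to every child, and a rule for counting an unscheduled visit that replaces a scheduled one within 48 hours;
- (b) test-confirmed malaria and LRTI defined by respiratory rate, each reported separately from diarrhoea;
- (c) unscheduled visits per child by group, and the share of them that end in no study disease;
- (d) reported cough taken from scheduled visits only.

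State that a null all-visit result for RUTF will be interpreted in the light of (a) to (c).

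The cost is small. History and examination are already planned at every scheduled visit, although uniform disease checks ask somewhat more than the rapid examination now allowed. The rest is endpoint wording and a little more analysis. The scheduled-visit comparison will have fewer events and less precision, and diarrhoea reporting at those visits remains open to the product incentive, which is why (b) is needed alongside (a).
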